### **3.2 Target population**

People with USI after prostate surgery (radical prostatectomy or TURP), for whom surgery is judged appropriate, are the target population. For the purposes of the trial we will define people with mild incontinence as those not requiring surgery. There is no clear threshold for defining moderate or severe incontinence and no clear evidence of differential benefit for either intervention according to degree of incontinence. We will therefore include all people whose incontinence is considered, from both the patient and surgeon perspectives, to require surgery.

### **3.3 Setting**

Participants will be recruited from NHS secondary care urological centres throughout the UK. Discussions at a number of meetings facilitated by the relevant professional organisation, British Association of Urological Surgeons (BAUS), has gained consensus from urologists that they would be willing to randomise participants to either option. Participants will be referred by their oncological urologist, specialist cancer nurse or local urologist or continence advisor. The BAUS Section of Oncology and the Section of Female Neurological and Urodynamic Urology have been kept fully involved during the planning of this trial and have given the study their full support. However, the applicants have collaborations with colleagues throughout Europe, particularly in Belgium and The Netherlands and the protocol would be made available for their participation, if agreed, and separately funded.

### **3.4 Planned Interventions**

Two surgical operations for male UI, the experimental technique of synthetic male sling, and the standard technique of AUS implantation will be evaluated. Divergence from pre-specified choices will be documented with reasons. All other operative variables will be described using standardised data collection forms. The surgical options have been agreed and standardised by consensus within the research team and with the recruiting urologists.

#### **3.4.1 Male Synthetic Sling (Male Sling)**

The male sling costs approximately £6000 per procedure (NHS tariff + device cost of £2000) with a typical 1-day hospital stay. It is placed under the urethra to elevate it and is held in place by passing it through the obturator foramina of the pelvic bone

bilaterally. It has a passive mode of action. The aim is to stop the loss of urine on exertion and the operation is effective immediately.

### **3.4.2 Artificial Urinary Sphincter (AUS)**

The artificial urinary sphincter (AUS) costs approximately £9000 per procedure (NHS tariff + device cost of £4500) with a typical 2-day hospital stay. It consists of an inflatable cuff placed around the urethra, a pressure regulating balloon to keep the cuff inflated, and a pump, placed in the scrotum, that the patient squeezes when they need to void. The aim is to close the urethra so that the patient is dry except when they wish to void. Once implanted the device is deactivated in the open position for a period of approximately four to six weeks to allow post-operative swelling to subside. The patient then returns to hospital for the device to be activated and to ensure that they are able to use the device correctly.

## **3.5 Planned inclusion/exclusion criteria**

### **3.5.1 Inclusion criteria**

1. Adult men who have decided in discussion with their urologist to have surgery for urodynamic stress incontinence (USI) resulting from prostate surgery.
2. Men who are willing to be randomised between male sling and AUS.

### **3.5.2 Exclusion criteria**

1. Men who have had previous male sling or AUS surgery.
2. Men with unresolved bladder neck contracture or urethral stricture after prostate surgery.
3. Men who do not consent to be randomised.
4. Men with insufficient manual dexterity to operate AUS device.
5. Men who are unable to give informed consent or complete trial documentation.

## **3.6 Allocation to trial groups**

All eligible men referred for consideration of incontinence surgery will be identified by the consultant, dedicated research nurse, or designated team member at pre-assessment clinics, urodynamic clinics, and outpatient urology clinics in each centre. The consultant/ research nurse will introduce the trial to the patients and, if interest is expressed, provide details of the trial by means of the Patient Information Leaflet (PIL). Each patient will have the opportunity to discuss the trial with the local clinical team. Patients may make a decision to participate during this consultation, at a separate appointment, at a pre-admission clinic or while at home or on admission for their operation. Men who agree to be contacted at home may receive a telephone call from the local Research Nurse to discuss any queries. Patients who decide to participate following telephone counselling can either send their completed documents (consent and baseline questionnaire) through the post to the local team at their treating hospital or bring it with them if they are returning to hospital for another consultation or treatment. 24 hr pads will also need to be taken into hospital for weighing at clinic visits, on the day of operation or information about the pad weight collected by phone prior to this date.

Each man will be asked for his signed informed consent to be randomised and followed up after surgery by postal questionnaires and clinical review. The PIL and the consent form will both refer to the possibility of long term follow up and being contacted about other research if the man is willing eg data collection from hospital and NHS records, including Office of National Statistics (ONS) and NHS central registers.

All participants who enter the trial will be logged with the central study office and given a unique Study Number. Randomisation will utilise the existing proven remote automated computer randomisation application at the study administrative centre in the Centre for Healthcare Randomised Trials (CHaRT, a fully registered UK CRN clinical trials unit) in the Health Services Research Unit, University of Aberdeen. This

randomisation application will be available both as a telephone based Interactive Voice Response (IVR) system and as an internet based service.

Randomisation will be computer-allocated and minimised on:

- type of prostate surgery (radical or TURP);
- whether or not they have had radiotherapy in addition to surgery
- centre.

All participants who consent to enter the trial will complete baseline questionnaires, including measurement of urinary and sexual symptoms, a urinary bladder diary, and have an objective 24 hour pad test carried out prior to randomisation. Participants who consent to randomisation will then be randomised to receive a male sling or AUS.

### **3.7 Methods to protect against sources of bias**

#### **3.7.1 Randomisation (avoiding selection bias)**

Participants will be logged and registered on the trial database prior to trial entry. Randomisation will be by secure remote third-party either via computer allocation using a web application or telephone. Randomisation will be carried out as close to the time of surgery as is practical, taking into account the standard procedures in each centre for ordering implants and arranging theatre schedules.

#### **3.7.2 Ensuring standardisation of intervention and outcome measurement (performance bias)**

**Investigators:** The basic acceptance criteria for participating urologists is that they must be uncertain regarding the best operative technique for the majority of patients, and they must be competent to perform the operations to be compared (i.e. beyond the learning curve), as judged by themselves and/or trial appointed trainers. The investigators are specialist urologists who will be responsible for recruiting and randomising men. All will be experienced in performing both operations, or if a surgeon performs only male sling or AUS, then he/she will be 'paired' with a local urologist who performs the other procedure, thereby guaranteeing that all participants will be operated on by the surgeon experienced in the operative technique to which he is randomised.

**Standardisation of surgical techniques:** The surgical procedures and other operative variables have been standardised as much as possible by using agreed protocols developed by the urological grant holders (Professors [name], [name], [name] and [name]). Any deviations from agreed protocols will be recorded. All investigators are experienced urological surgeons. Investigators, who are experienced in male sling surgery, will deliver any additional training if required. The clinical grant applicants will ensure standardisation of existing techniques and outcome measures, including the use of new devices.

The research nurses and/or the surgeons will complete a Theatre case report form (CRF) at the time of surgery, to ensure a complete record of all surgical techniques and materials used, and any intra-operative difficulties or complications. The research nurses in each centre will ensure completeness and accuracy of data entry using remote data capture via a trial web-based portal at the Study Office in Aberdeen, authored and managed by the Centre for Healthcare Randomised Trials (CHaRT), the UK CRN-registered trials unit in Aberdeen.

As this is a pragmatic trial, postoperative care will be according to local centre practice, but clinical and resource-use data will be recorded.

#### **3.7.3 Loss to follow up (attrition bias)**

Loss to follow-up in our previous trial of conservative treatment for men with UI after prostate surgery (Glazener 2011a, Glazener 2011b) was 5 to 10% at one year.

However, a less optimistic estimate of 15% loss to follow up has been used in the sample size calculations. We will take very active measures to minimise such loss, such as phoning the participants, using retention incentives and checks with their GPs. In addition we will obtain consent from the participants to enable us to access centrally-held NHS data, for example via the NHS Strategic Tracing Service in England and Wales, and using CHI numbers from the Information Services Division in Scotland.

### **3.7.4 Other sources of bias (detection bias)**

After randomisation, participants will not be told of their allocation before surgery unless they specifically request this information. Blinding in theatre is not possible given that this is a surgical procedure trial with different implantation devices. After surgery, group allocation cannot be concealed from the participant or the ward staff due to the nature of the device. Outcome assessment is largely by participant self-completed questionnaire, so avoiding interviewer bias.

Research staff will be blinded to allocation while conducting data collection for outcomes (e.g. pad test weighing), performing data entry and analysis, and by using Study Numbers only to identify participants, questionnaires, diaries and pads. Participants will be asked not to reveal information about their surgical treatment. Staff will be asked to record whether or not they knew which operation was performed before undertaking outcome assessments. All participants will be actively followed up, with analysis based on the intention-to-treat principle. All analyses will be clearly predefined to avoid bias.

## **3.8 Sample size**

There is a lack of robust evidence from comparative studies on which to base the trial sample size calculation. For the primary outcome (incontinence), limited evidence from case series suggests that 20% of people would still be incontinent 12 months after AUS. For male slings, after primary implantation the percent of people incontinent is thought to be 35%.

For our chosen non-inferiority comparison at 12 months, a trial with 310 participants will allow us to be 90% sure that the lower limit of a two-sided 95% confidence interval will exclude the possibility that the AUS is more effective by a margin of 15% or more. Allowing for 15% loss to follow-up after enrolment we plan to recruit 180 participants per group into the trial. This sample size will allow the detection of a difference equivalent to 0.25 of a standard deviation (SD) at 80% power between the groups for the key secondary outcome, ICIQ at 24 months.

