## **2 THE QUESTIONS WHICH THIS STUDY WILL ADDRESS**

The aim of the trial is to determine whether the male sling is non-inferior to implantation of the AUS for people who have UI after prostate surgery (for cancer or benign disease), judged primarily on clinical effectiveness but also considering relative harms and cost-effectiveness. In order to determine whether the male sling or AUS is cost-effective for the NHS in the UK, the interventions will be compared in terms of: incontinence in men after prostate surgery; the relative harms of the interventions; costs to the patients, and to the NHS including the need for repeat surgery in both groups; and overall patient satisfaction.

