## **APPENDIX 1 BACKGROUND TO THE STUDY**

### **A1.1 Introduction**

The male synthetic sling (male sling) is an alternative to the artificial urinary sphincter (AUS) for people with urodynamic stress incontinence after prostate surgery, but there is limited evidence of relative effectiveness and cost-effectiveness to guide choice. We aim to resolve this by directly comparing the rate of incontinence at 12 months in a non-inferiority randomised trial powered on the basis that people would accept up to 15% lesser effectiveness in return for easier device operation and possible reduced adverse effects. We will recruit all patients who have decided, with their clinicians, that surgery is needed. To address feasibility of recruitment, we have devised a schedule to give early indication of our ability to recruit to target but avoiding any disruptive pause if we are successful.

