### **A1.3 Evidence for surgical management for men with urinary incontinence after prostate surgery**

There are no published RCTs comparing male slings with AUS. A Cochrane Review found only one small poor-quality RCT of surgery which suggested that implantation of artificial urinary sphincter (AUS) was better than an injectable bulking agent (Imamoglu 2005). In this RCT, the men treated with AUS were more likely to be cured (18/20, 82%) than those who had the injectable treatment (11/23, 46%, OR 5.67, 95% CI 1.28 to 25.10). All other evidence comes from case series which were recently summarised by the WHO-sponsored 4th International Consultation on Incontinence (Herschorn 2009). This reported that the median (range) cure rate after AUS was 82% (59 to 90%, 12 series) and for male sling was 63% (13 to 86%, 20 series) (Silva 2011). A more recent review of the literature looked at six case series of men implanted with the Advance® brand of male sling and reported a cure rate of 60% (de Ridder 2011). More recently sub-group analysis from a large case series showed that at three years after sling implantation, men categorised on the basis of pad usage as having “mild/moderate” incontinence, had a cure/improved rate of 82% and those arbitrarily categorised as having severe incontinence had a cure/improved rate of 67% (Rehder 2012). These similar cure rates, which lie within the previously reported range for all degrees of incontinence, support our intention of not using the degree of incontinence

as an eligibility criterion. Results from a further recent case series suggests that the outcome of implantation of AUS is not compromised by previous insertion of a male sling (Lentz 2012). As it is likely that some men in our trial, randomised to sling, may require subsequent repeat surgery, it is reassuring that their ultimate outcome is unlikely to be worse than those randomised to AUS.

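### Section 3.8 claims 90% power, but with AUS at 20% this needs a sling incontinence rate of about 20%; at the 35% printed beside it the power is 2.5%

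*Protocol*

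**What the plan says.** Section 2 sets the hypothesis: "The aim of the trial is to determine whether the male sling is non-inferior to implantation of the AUS". Section 3.8 then gives the evidence for the sample size. For the control arm, "limited evidence from case series suggests that 20% of people would still be incontinent 12 months after AUS". For the experimental arm, "For male slings, after primary implantation the percent of people incontinent is thought to be 35" per cent. No other rates appear in the section.

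The next paragraph makes the power claim: "a trial with 310 participants will allow us to be 90% sure that the lower limit of a two-sided 95% confidence interval will exclude" a 15-point advantage for AUS. After allowance for 15% loss to follow-up, the recruitment target is 180 per group.

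Appendix A1.1 repeats the margin and its rationale, describing the trial as "powered on the basis that people would accept up to 15% lesser effectiveness in return for easier device operation". Neither place states the true difference between the arms at which the 90% was calculated.

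**The concern.** The power of a non-inferiority trial depends on the true difference assumed as well as on the margin. Section 3.8 gives a margin of 15 points and two rates that differ by 15 points. A reader who takes those rates as the inputs, as the layout of the section invites, puts the true difference exactly on the margin. The chance of showing non-inferiority is then the one-sided error rate, not 90%.

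The primary conclusion turns on this comparison. Section 3.1 says a sling that is inferior by at least the margin would probably not be adopted across the NHS, and that within the margin cost-effectiveness decides. Section 6.1.2 makes the 12-month outcome against the margin a major consideration for the DMC. Those reading the power statement need to know which true sling rate it refers to.

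**Working it through.** **Inputs (section 3.8).** Margin 15 points; two-sided 95% interval, so 1.96; 90% power, so 1.2816; 310 men analysed, 155 per arm. Rates: AUS pA = 0.20, sling pS = 0.35.

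**Formulas.**

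n per arm = (1.96 + 1.2816)² × [pA(1−pA) + pS(1−pS)] / [0.15 − (pS−pA)]²

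Power = Φ( [0.15 − (pS−pA)] / SE − 1.96 ), with SE = √{[pA(1−pA) + pS(1−pS)] / 155}

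**Step 1: reproduce 310.** The stated size follows if both arms share a rate of 20% to 21%.

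- 20% in both: 10.51 × 0.32 / 0.0225 = 149.4, so 150 per arm, 300 in total (306 by the Farrington-Manning method). Power with 155 per arm is 91.0%.
- 21% in both: 10.51 × 0.3318 / 0.0225 ≈ 155 per arm, 310 in total. Power is 90.0%.

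Other routes miss 310. Equal rates of 27.5% or 35% need 374 or 426. A superiority test of 20% v 35% at 90% power needs 370. Two variants come close, but only by dropping the stated 90% power or the two-sided 95% interval: a one-sided 5% test at an equal 27.5% (304), and superiority of 20% v 35% at 80% power with continuity correction (302).

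**Step 2: the printed rates.** At 20% v 35%, 0.15 − 0.15 = 0, so power = Φ(−1.96) = 2.5%. The sample size multiplies a zero and drops out: 153, 155 and 180 per arm all give 2.5%. Exact binomial enumeration with 155 per arm also gives 2.5%.

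**Step 3: between the two (AUS 20%, 155 per arm).**

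| True sling rate | 0.15 − difference | SE | Power |
|---|---|---|---|
| 20% | 0.15 | 0.0454 | 91% |
| 22% | 0.13 | 0.0463 | 80% |
| 25% | 0.10 | 0.0473 | 56% |
| 30% | 0.05 | 0.0489 | 17% |
| 35% | 0 | 0.0500 | 2.5% |

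Solving for 90% power with AUS at 20% gives a sling rate of at most 20.2%. For comparison, 90% power would need 366 per arm if the sling rate were 25% and 1,556 per arm if it were 30%.

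**Step 4: attrition.** 360 × 0.85 = 306 analysed, slightly under 310. Power at an equal 20% is then 90.7%, so attrition does not explain the discrepancy.

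**The case against.** *Equal rates are conventional.* Non-inferiority trials are often powered on no true difference, and applying the printed AUS rate to both arms gives 300 to 306, close to 310. This stands: a reader might infer that 310 is miscalculated, and it is not. But the convention has to be stated, above all when a different sling rate is printed as evidence for the same calculation.

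*The 35% is tentative and is not the intention-to-treat rate.* The section admits that robust comparative evidence is lacking, and it gives the sling figure as a belief about results after primary implantation. Sections 3.7.4 and 6.1 specify intention-to-treat, so men given an AUS after a failed sling stay in the sling arm. Appendix A1.3 expects some repeat surgery, with final outcomes unlikely to be worse than after AUS. This too has force: the rate by allocation could be below 35%. The protocol does not say how far below at 12 months and does not use the argument to support its power. A fall to 25% would still leave 56%.

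*The 90% is not confined to 20–21%.* Lower equal rates, a sling rate better than AUS (25% AUS v 23.5% sling: 92%) and some low-rate pairs (10% v 13%: 91%) also reach it. That is correct, and the point is therefore made with AUS fixed at the 20% that section 3.8 prints.

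*The appendix medians.* A reader might subtract the median cure rates in A1.3 (82% and 63%) and infer a 19-point deficit, already beyond the margin. The documents do not support this. The medians come from separate, non-comparative series with wide, overlapping ranges (59 to 90% and 13 to 86%), and A1.3 does not define cure, whereas the trial counts any reported leakage (section 5.1.1).

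**Conclusion.** The point holds as an internal contradiction between the stated power and the rates printed beside it. With AUS at 20%, 155 analysed per arm, a 15-point margin and a two-sided 95% interval, 90% power requires a true sling rate of about 20% or lower. At the printed 35% it is 2.5%, and no sample size would raise it. The calculations use the unpooled normal approximation; exact enumeration agrees at 20% v 20%, 20% v 25% and 20% v 35%.

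Two stronger inferences should not be drawn. The protocol does not establish that failing to show non-inferiority is the expected result, because 35% is a tentative figure that may exceed the sling-arm rate by allocation. Nor is the trial's eventual conclusion compromised: the confidence interval is valid whatever rates were assumed in planning.

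**What to change.** Reword the power statement in section 3.8 to say that 310 analysed men give about 90% power if the true 12-month incontinence rate is about 20% in both groups. Add that the 35% quoted for slings is not the alternative for which the trial is powered. With AUS at 20%, give the power at sling rates of 25%, 30% and 35%: 56%, 17% and 2.5%.

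The cost is a few lines of text and a less favourable-looking power statement. The number enrolled, the margin and the analysis do not change.

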## **4 SUBSEQUENT ARRANGEMENTS**

### **4.1 Informing key people**

Following formal trial entry:

The Study Office will:

- i) inform the participant's General Practitioner (GP) (by letter) enclosing information about MASTER and the Study Office contact details.

The local Research Nurse/Recruitment Officer and/or urologist will:

- i) file the Hospital Copy of the Consent form in the hospital notes along with information about MASTER.
- ii) inform the ward and theatre staff as appropriate of the participant's entry to the trial and details of the intervention allocation (theatre only).
- iii) use the MASTER internet database to enter data regarding the participant, including data required to complete randomisation; and intra-operative and postoperative information abstracted from local medical records.

- iii) Maintain and archive Study documentation at the site. A copy of the signed consent form is returned to the Study Office in Aberdeen after database entry.

## **4.2 Monitoring the participants**

Participants will be contacted by phone, post or email as appropriate. In case of non-return of questionnaires, or non-attendance at outpatient appointments, attempts will be made by staff at the Study Office to trace the participant directly using these means or indirectly by contacting the GP.

